#### 2.10.5. Safety Assessment

Vital signs, ECG, and laboratory tests (liver and kidney function and blood and urine routine examination) will be compared before and after interventions, and the safety of the interventions will be assessed when AR is controlled. The subjects should contact the researchers if any side effects or adverse events occur. After receiving the patient's feedback, investigators will inform the subjects to visit the hospital for further assessment. In addition, a urine pregnancy test should be performed before female subjects of childbearing age are recruited.

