### 2.9. Interventions

#### 2.9.1. Experimental Group

MYN is produced and packed by Sichuan Purity Pharmaceutical Co., Ltd. To ensure the stability of the drug, the same batch of drugs will be used in this study (drug batch number: 051–210917). MYN is currently under patent review. We have uploaded all of the specific components, dosage, and other information of MYN to the official website of China National Intellectual Property Administration, which is open for access and can be found on the patent search and service system page of the official website of China National Intellectual Property Administration [28] via publication no.: CN109908209A. MYN will be administered intranasally and two pumps/nostril will be sprayed twice daily. The drug will not be administered once the patient meets the clinical control standard for two weeks. The shortest treatment time will be not less than four weeks, and the longest treatment time will be not more than three months.

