#### 2.9.3. Clinical Control Standard

After the subjects start treatment, the rhinitis control assessment test (RCAT) will be applied every week for each subject. If the RCAT score is >21, AR is well controlled (clinical control standard); if the RCAT ≤21, it is not controlled.

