### 2.12. Statistical Methods

All analyses will be based on the intention-to-treat (ITT) principle. Missing data will be reduced to a minimum. For data loss caused by subject drop-out, data from the previous measurement will be carried forward. The frequency, percentages, means and standard deviations, medians, and quartiles will be calculated for descriptive analysis. Intergroup comparisons of continuous variables will be performed using the *t*-test or Mann–Whitney *U* test. Categorical variables will be compared using Pearson *χ*^2^ tests or Fisher exact tests. Time-to-event outcomes will be analyzed using the Kaplan–Meier method and Cox proportional hazard models. Two-tailed *p* < 0.05 will be considered statistically significant for all analyses. All statistical analyses will be conducted using SPSS version 25.0 for Windows (IBM Corporation, Armonk, NY, USA).

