### 2.15. Criteria for Adverse Event Reporting and Discontinuing or Modifying the Allocated Interventions

Subjects may refuse to participate in the study or withdraw from the study at any time during the study without affecting their medical treatment and benefits. If a patient is uncooperative, the investigators can also end the patient's participation in this study. The investigators will make a follow-up appointment (by phone, e-mail, and message), contact the subject if possible, inquire about the reason for withdrawing, the time of last medication, and complete as many assessment items as possible. If any adverse event (AE) occurs during the trial, the responsible investigator should take the necessary measures to provide treatment. Any serious adverse events (SAEs) will be reported within 24 h to the sponsor and the ethics committee. The manifestation, severity, onset time, duration, and prognosis of the adverse events will be observed and recorded in detail. A committee of medical experts will determine whether it is related to the treatment. In the case of AE and injuries caused by diagnostic tests or research drugs, effective measures should be taken to ensure the safety of the subjects. Moreover, the research team will pay the related treatment costs and the corresponding economic compensation according to China Good Clinical Practice Guideline.

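### Section 2.10.5 gives two triggers for the post-treatment safety tests, one tied to rhinitis control, and the carry-forward rule in 2.12 would record untested drop-outs as unchanged

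*Protocol article*

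**What the plan says.** All places are in the protocol article.

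- **2.10.5, Safety Assessment.** One sentence carries two time references. Vital signs, ECG and laboratory tests "will be compared before and after interventions", and "the safety of the interventions will be assessed when AR is controlled".
- **2.9.3, Clinical Control Standard.** Control is a score on the patient-reported scale: "If the RCAT score is >21, AR is well controlled (clinical control standard); if the RCAT ≤21, it is not controlled".
- **2.9.1, Experimental Group (2.9.2 has the same rule for the control arm).** Treatment can end in two ways. One is through control: "The drug will not be administered once the patient meets the clinical control standard for two weeks". The other is the time limit: "the longest treatment time will be not more than three months".
- **Note to Table 3.** Drug withdrawal is defined only as the point at which control has lasted two weeks. The body of the table is not shown.
- **2.12, Statistical Methods.** "All analyses will be based on the intention-to-treat (ITT) principle". On missing data: "For data loss caused by subject drop-out, data from the previous measurement will be carried forward". Safety data are not excepted from either rule.
- **2.15.** When a subject withdraws, the investigator is to make contact and "complete as many assessment items as possible". Adverse events are recorded in detail, without reference to control.

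**The concern.** Safety is a stated aim alongside efficacy, and the scheduled ECG and laboratory tests are there to find changes that a patient would not notice or report. Two features of the text weaken that comparison.

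First, the time of the post-treatment test is partly defined by an efficacy state. Read literally, the control-based trigger never fires for a patient who uses the spray for the full three months without control, although that patient has the longest exposure. Nor does it fire for a patient who stops early before reaching control.

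Second, carrying the previous value forward is a particularly poor choice for a safety variable measured once before and once after treatment, because the only value available to carry is the pre-treatment one. The rule then supplies a result of no change for a drop-out who was never tested on or after treatment. If some of these patients left because of harm, the before/after tables look more reassuring than the data justify.

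**Working it through.** The plan gives no figure for this point: no rate of non-control, of early stopping or of missing safety tests. There is nothing to reproduce, and the sample size is unaffected. The check is a comparison of the passages, followed by arithmetic over assumed shares.

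**Step 1: which trigger covers whom**

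| How treatment ends | After-intervention trigger (2.10.5) | Control trigger (2.10.5) | Carry-forward (2.12) |
|---|---|---|---|
| Control held for two weeks | covered | covered | not needed |
| Three-month limit, uncontrolled | covered if this phrase governs | not covered | does not apply: not a drop-out |
| Drop-out before control, tested at withdrawal | test obtained | not covered | not needed |
| Drop-out before control, not tested | no test | not covered | applies: baseline carried forward |

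The two phrases agree only for the first row. Even there the day may differ, because the note to Table 3 separates the point of reaching control from drug withdrawal two weeks later.

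**Step 2: what carry-forward does in the last row**

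With one measurement before treatment and one after, the previous measurement for an untested drop-out is baseline. The entered change is baseline minus baseline, which is 0.

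**Step 3: effect on the mean change**

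Let d be the share of an arm with baseline carried forward, m1 the true mean change in tested patients and m2 the true mean change in untested patients.

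- Observed mean change = (1 - d) × m1 + d × 0
- True mean change = (1 - d) × m1 + d × m2
- Ratio = (1 - d) × m1 / [(1 - d) × m1 + d × m2]

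If m2 = m1, the ratio is 1 - d. With 190 / 2 = 95 patients per arm:

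| Assumed d | Patients per arm | Ratio, m2 = m1 | Ratio, m2 = 0.5 × m1 | Ratio, m2 = 2 × m1 |
|---|---|---|---|---|
| 5% | 95 × 0.05 = 4.75, about 5 | 0.95 | 0.95 / 0.975 = 0.97 | 0.95 / 1.05 = 0.90 |
| 10% | 95 × 0.10 = 9.5, about 10 | 0.90 | 0.90 / 0.95 = 0.95 | 0.90 / 1.10 = 0.82 |

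So (1 - d) is not a bound. The loss is smaller if untested patients change less, for example after shorter exposure, and larger if they change more.

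**Step 4: effect on a count of new abnormalities**

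As an illustration, assume new abnormalities in 5% of tested and 15% of untested patients, with d = 10%.

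- Observed: 0.90 × 5% = 4.5%
- True: 4.5% + 0.10 × 15% = 6.0%

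All the shares and rates in steps 3 and 4 are assumptions.

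**The case against.** The strongest reply has four parts.

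1. **The first half of the sentence in 2.10.5 already asks for an after-intervention test, with no condition on control.** This is fair, and it is probably the intention. It does not settle the matter, because the second half states a different condition and the note to Table 3 also defines withdrawal through control.

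2. **Harm is captured by other routes.** Subjects are told to report side effects and are called in for assessment, investigators try to complete assessments at withdrawal, and adverse events are recorded whatever the control status. This stands, and it rules out any claim that harmful cases disappear from the trial. It does not rescue the scheduled comparison: the withdrawal assessment is best effort and names no safety test, and the extra visit depends on the patient reporting something, whereas laboratory and ECG changes can be silent.

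3. **The visit schedule is in a table that is not shown, and a fuller protocol or analysis plan may exist.** The table may fix an end-of-treatment visit or add safety time points, so the statement that baseline is the only earlier value rests on the visible text. The carry-forward rule itself is not a detail left to another document. It is written here and covers all analyses.

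4. **The size cannot be derived from the plan.** Correct. The 10% allowance in section 2.6 is overall loss to follow-up, which includes the six months after withdrawal, when the post-treatment tests should already have been done. It is not an estimate of the untested share.

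A reader might also infer that patients who never reach control are entered with unchanged values. The text does not support that. Carry-forward is limited to drop-out, and someone who completes three months uncontrolled has not dropped out. Their test time is ambiguous, or their result is missing, but it is not filled in.

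**Conclusion.** The point holds in two limited parts. The wording of 2.10.5 contains two triggers that do not cover the same patients, and only one of them reaches those who end treatment without control. Independently, the carry-forward rule in 2.12, applied as written, gives untested drop-outs a change of zero in vital signs, ECG and laboratory values, and so biases the before/after comparison towards no change.

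The size is unknown. With equal true mean change in tested and untested patients, the observed change would be 0.95 of the truth at an assumed 5% untested and 0.90 at an assumed 10%. It would be closer to the truth if untested patients change less, and further from it if they change more. The conclusion assumes that some drop-outs are not tested at withdrawal and that the unseen table adds no safety measurement between baseline and the end of treatment. It concerns the scheduled safety measurements only. Adverse-event reporting, the primary outcome and the sample size are not affected. It should be corrected, as a repair of wording rather than of design.

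**What to change.** - **2.10.5:** reconcile the two phrases so that the post-treatment vital signs, ECG and laboratory tests already planned are tied to the end of treatment for every treated patient, whether treatment ended through control, at the time limit or early. Align the note to Table 3.
- **2.12:** exclude safety data from carry-forward. Analyse observed values and shifts from normal to abnormal in treated patients, and report by arm how many were not tested and why.

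The treatment rules and the sample size stay as they are. The cost is an end-of-treatment visit for those who stop without control, and some safety values that remain visibly missing. Analysing observed values does not remove bias if untested patients differ from tested ones, which is why the count of untested patients per arm should be shown beside the results.

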## 1. Introduction

Allergic rhinitis (AR) is one of the most common allergic diseases worldwide and it is a global health problem affecting 40% of the world's population [1]. The prevalence of AR has been increasing worldwide since the 1960s [2] and has dramatically increased in recent years [3]. For example, AR showed a sharp increase in prevalence from 11.1% to 17.6% over 6 years in major Chinese cities [4]. The repeated attacks of AR are one of the main difficulties faced by patients. A study of 7-year-olds in South Korea found that the two-year recurrence rate for AR is 72% [5].

The pharmacotherapy of AR includes corticosteroids, antihistamines, and decongestants, most of which focus on suppressing immune factors and controlling immediate symptoms. Even though pharmacotherapy has proven to be highly effective in controlling allergic symptoms, most of the pharmacological management approaches recommended in the guidelines for AR have not been evaluated for efficacy in controlling recurrences. Furthermore, their long-term use can cause side effects, including epistaxis, mucosal dryness, and other adverse reactions, reducing patient compliance. Globally, while the standard pharmacotherapy of AR is relatively mature, the prevalence of AR is still rising [6, 7], and the recurrence rate is still high [8], making it urgent to find new therapies to solve this problem.

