#### 2.10.2. Primary Outcomes

The primary outcome is the six-month recurrence rate of AR after intervention withdrawalFollow-up: subjects will enter the follow-up period after withdrawal of medications. Once a relapse occurs, the patient's recurrence time will be recorded, and the follow-up ends. Otherwise, the follow-up will continue until six months after drug withdrawal.Definition of recurrence/relapse: when the RCAT score ≤21 during follow-up, the patient will be considered in a relapse stateDefinition of six-month recurrence rate: six-month recurrence rate = number of recurrent AR patients in six months/total number of patients × 100%The RCAT has sufficient reliability, validity, and responsiveness and is a simple patient self-assessment scale [29]. RCAT can be used to assess a patient's rhinitis control status in clinical practice [30]. During the treatment stage, we will collect the RCAT scale online once a week, and during the follow-up stage, we will collect the RCAT scale online every two weeks.

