## 3. Discussion

Mometasone furoate aqueous nasal spray will be administered to the control group in this study. Intranasal corticosteroids (INCs) are first-line treatments for persistent or moderate-severe AR patients [32]. INCs are effective for the four significant classic symptoms of AR and ocular symptoms of AR [1]. INCs are more effective than H1-antihistamines and leukotriene receptor antagonists, especially for nasal obstruction [32]. The mechanism of action is related to the local anti-inflammatory effect of nasal mucosal cells. Second-generation INCs further minimize systemic bioavailability (<1%) compared with first-generation INCs and oral corticosteroids [33], thereby limiting systemic effects on AR. Some studies have shown that AR is a local reaction of systemic inflammation and systemic immune inflammation of multiple organs and systems caused by allergen invasion [34]. The existence of systemic inflammation will keep the body in a sensitized state, and it is easily restimulated when encountering allergens, resulting in recurrence. Therefore, the insufficient systemic efficacy of INCs also limits their efficacy in controlling recurrences.

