Limitations: this study also has limitations. For example, MYN is a nasal spray made from pure Chinese medicine. It is brown and has a light herbal odor, while the mometasone furoate aqueous nasal spray is colorless and odorless, so it is difficult to blind subjects to treatment. Therefore, this study adopts an open-label design, but this may cause bias in evaluating the efficacy of relapse control. Nasal endoscopy examination will be conducted on subjects before and after interventions to objectively reflect the efficacy of the interventions and minimize the influence of psychological effects on subjects in an open-label design. Efforts to make MYN colorless and odorless are ongoing.

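### Local nasal adverse events rest mainly on spontaneous reports by unblinded patients, and the planned endoscopy has no stated safety use, so these events may be under-reported, and unequally between arms

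*Protocol article*

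**What the plan says.** Safety is in the title and in section 2.1 (Objectives). Section 2.10.5 sets out how it is measured:

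- Scheduled tests: "Vital signs, ECG, and laboratory tests (liver and kidney function and blood and urine routine examination) will be compared before and after interventions".
- A general assessment: "the safety of the interventions will be assessed when AR is controlled". What it consists of is not stated.
- Other adverse events: "The subjects should contact the researchers if any side effects or adverse events occur". The next step is: "After receiving the patient's feedback, investigators will inform the subjects to visit the hospital for further assessment".

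Section 2.8 blinds outcome assessors, examiners and data analysts, but not patients or researchers. The Introduction says of existing drugs for allergic rhinitis that "their long-term use can cause side effects, including epistaxis, mucosal dryness, and other adverse reactions, reducing patient compliance".

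Two scheduled procedures could carry local safety information:

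- Online forms (section 2.10.2): "During the treatment stage, we will collect the RCAT scale online once a week", and every two weeks in follow-up.
- Endoscopy, listed as a secondary outcome in section 2.10.3. The Discussion gives its purpose: "Nasal endoscopy examination will be conducted on subjects before and after interventions to objectively reflect the efficacy of the interventions".

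**The concern.** Both products are sprayed into the nose, so local tolerability is an obvious part of any safety comparison. The named tests look elsewhere. For the comparator's class the Discussion itself expects little systemic exposure: "Second-generation INCs further minimize systemic bioavailability (<1%) compared with first-generation INCs and oral corticosteroids".

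For symptomatic events the stated route depends on a patient who knows the arm deciding to contact a researcher who also knows it. Mild nosebleeds or stinging may go unmentioned, and willingness to mention them may differ between a known steroid and a known herbal product. The limitations paragraph acknowledges open-label bias for relapse and offers endoscopy as a safeguard for efficacy. It offers nothing comparable for safety. At stake is whether a statement that one spray is better tolerated, or that neither causes local harm, reflects the drugs or reflects who chose to report.

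**Working it through.** **1. What each stated source can show about local nasal events**

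| Source | Timing | Local nasal events? |
|---|---|---|
| Vital signs, ECG, laboratory tests (2.10.5) | Before and after treatment | No; all systemic |
| Safety assessment (2.10.5) | When rhinitis is controlled | Unknown; content not stated |
| Patient contact (2.10.5) | Whenever the patient chooses | Yes, if reported; unblinded |
| Detailed recording and expert causality review (2.15) | After an event is known | Cannot recover an unreported event |
| Endoscopy (2.10.3, Discussion) | Before and after treatment, and at relapse | Could show mucosal changes; may miss bleeding between visits; no safety use stated |
| Online RCAT (2.10.2) | Weekly, then every two weeks | No adverse-event item stated |

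The only row that states a method for capturing local symptoms is patient-initiated contact.

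**2. Is there a plan figure to reproduce?** Not on this point: the article gives no local event rate and no reporting fraction. Its one design figure, 86 per group, does reproduce: (0.75×0.25 + 0.50×0.50)×(1.960 + 0.842)² / (0.25 − 0.05)² = 85.9, rounded up to 86. It has no bearing here. The illustrations below take only 190/2 = 95 per arm from the plan.

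**3. Effect of unequal reporting (all rates assumed).** Observed rate = true rate × fraction reported. If the true rates are equal, the observed ratio is simply the ratio of the two reporting fractions, whatever the true rate.

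- True rate 15% in both arms (95×0.15 = 14.25 events each), with 30% and 60% reported: 0.15×0.30 = 4.5% and 0.15×0.60 = 9.0%. The ratio is 0.5.
- True rates of 5%, 10% and 20%, same fractions: expected counts of 1.4 and 2.9, 2.9 and 5.7, 5.7 and 11.4. The ratio is 0.5 each time.
- Fractions swapped: the ratio is 2.0.

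**4. Effect of equal under-reporting (assumed).** With 50% reported in both arms, expected counts per arm at true rates of 5%, 10% and 20% fall from 4.8, 9.5 and 19.0 to 2.4, 4.8 and 9.5. The ratio stays at 1.0, but a real difference becomes harder to see. For an assumed true 5% against 15%, two-sided 5%, n = 95 per arm, power is Φ(z) with

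z = [|p₁ − p₂| − 1.96·√(2p̄(1 − p̄)/n)] / √[(p₁(1 − p₁) + p₂(1 − p₂))/n].

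- Full reporting: (0.10 − 1.96×0.0435)/0.0429 = 0.34, power 63%.
- 50% reported (2.5% against 7.5%): (0.05 − 1.96×0.0316)/0.0314 = −0.38, power 35%.
- By the same formula, 70% reported gives 47% and 30% reported gives 23%.

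These figures show how the mechanism works. They do not estimate what will happen in this trial.

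**The case against.** The strongest reply is that this is a condensed article. Section 2.14 refers to a CRF and an SOP, section 2.17 says the complete protocol is on the registry, and the Table 3 timeline is not visible here, so patients may well be asked about adverse events at visits. Asking patients to report problems between visits is ordinary practice and does not show that nobody asks them. That stands as a limit. It does not remove the point, because section 2.10.5 states a method, and no part of that method solicits local events.

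A reader might go further and infer that local harms are captured only if patients volunteer them, and that they will be under-counted. The documents do not support either inference:

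- A general safety assessment is scheduled, and its unstated content could include local symptoms.
- Endoscopy before and after treatment, with examiners blinded, could reveal mucosal damage.
- The Introduction links epistaxis and dryness to long-term use of existing drugs. Treatment here runs from four weeks to three months, and the article does not attribute these harms to MYN.
- No formal comparison of local tolerability is defined.

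Nor do the documents show that a hospital visit deters reports. Section 2.13 offers free examinations and compensation for follow-up visits, and section 2.15 covers treatment costs and compensation for adverse events caused by tests or study drugs. These could work the other way. Systemic monitoring of a herbal product is also reasonable in itself; the point is what the stated tests leave out.

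**Conclusion.** The point holds in limited form. As written, the article pairs systemic scheduled tests with spontaneous reporting by unblinded patients to unblinded researchers, and gives the planned endoscopy an efficacy purpose only. Local nasal events may therefore be under-reported, and reported unequally between arms.

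The size and direction of any bias cannot be derived from the documents. The ratios of 0.5 and 2.0 and the fall in power rest entirely on assumed event rates and reporting fractions. It would be wrong to infer that the bias favours MYN: the text gives no basis for a direction.

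The conclusion assumes that no solicited questioning exists in the full protocol, CRF or Table 3. If it does, the sponsor need only say so and align section 2.10.5. The primary outcome and sample size are unaffected. The change is worth making because the contacts and examinations it needs are already planned.

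**What to change.** 1. Add a short adverse-event question set, worded identically in both arms, to each online RCAT form, weekly on treatment and every two weeks in follow-up. It should cover nosebleed, dryness, irritation or burning, and any other problem.
2. At the endoscopies already planned, have the blinded examiner record bleeding, crusting, dryness and erosion, and designate these findings as safety data.
3. Report solicited local events by arm, separately from spontaneous reports. Keep the treatment period apart from follow-up, because follow-up ends at relapse and the number of forms will then depend on outcome.
4. State what the safety assessment tied to rhinitis control contains.

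**Cost.** A few questions on an existing form and a few fields on an existing record, with no new visit, procedure or staff. There are three downsides. Recorded adverse-event rates will rise in both arms. The answers remain self-report by unblinded patients, so prompting evens out ascertainment but does not remove expectation bias. Recruitment began on September 1, 2021, so the change needs an amendment approved by the funder and the ethics committees (section 2.17), and events before and after it must be reported separately because they were ascertained differently.
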